### Postoperative rehabilitation

For both surgical procedures (ACL-R with ST or QT-B grafts), patients will be followed by a physiotherapist that will follow the standardized rehabilitations protocols from the clinic and individualize the rehabilitation when needed for the specific patient. Participants will be allowed to fully weight bear the knee with the aid of crutches postoperatively in the event of isolated ACL-R and in ACL-R with meniscal resection, meniscal ramp lesion repair or meniscal bucket-handle repair. Individuals undergoing meniscal root repair will be allowed to partially weight bear for 6 weeks and those undergoing a repaired radial meniscal lesion will be instructed not to weight bear during the first 6 weeks. ROM will be restricted for all meniscal repair procedures initially to protect the meniscus early in the healing process. Surgically treated cartilage defects in the femuro-patellar region will be allowed to weight bear in the ROM restricted at 0–30 degrees with a knee orthosis, while surgically treated cartilage defects in the tibiofemoral region will be treated with partial weight bearing for 6 weeks. Postoperative weight-bearing and ROM restrictions will not be used as stratification variables, and no subgroup analyses will be performed based on these factors.

According to the standardized rehabilitation protocol, the rehabilitation progression follows a structured, criterion-based protocol rather than a purely time-based schedule. After the initial six weeks, patients transition through defined phases focusing on strength development, neuromuscular control, and functional capacity. From week 13–14 onward, there will be no restrictions on quadriceps training. Clearance to begin impact activities such as running will typically occur around 4 to 5 months postoperatively and requires ≥ 80% limb symmetry index (LSI) in quadriceps and hamstring strength, along with resolution of joint effusion. Return to sport (RTS) is generally assessed between 8 and 12 months and requires ≥ 90% LSI in both strength and hop testing, absence of swelling or functional complaints, and adequate movement quality during sport-specific tasks. Although adherence to the rehabilitation program will not be tracked, all functional tests are performed at standardized checkpoints using validated protocols to assess progression (Table 1). Tailoring of the rehabilitation program will be allowed based on the individual recovery and sport-specific demands.

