### Primary outcome

#### Knee Laxity at 6 months post ACL-R

Knee Laxity will be measured preoperatively and at 6 months postoperatively using the KT-1000 arthrometer® (MEDmetric®, Corp, San Diego, CA, USA) in accordance with the clinic’s standard routine for postoperative evaluation of ACL-R [10]. Patients will be positioned supine with the knee at approximately 20 degrees of flexion with the help of a bolster placed under the thighs, and with the feet are supported on a footrest to minimize muscle contraction and prevent external rotation. The contralateral (uninjured) knee will be tested first, followed by the ACL-injured knee. For each knee, three trials will be conducted using the standardized anterior force corresponding to 134 N (third audible “click” of the KT-1000). Between trials, the arthrometer will be recalibrated and the median value of the three valid measurements will be recorded for each side. The STS difference in ATT between the ACL-injured knee and the healthy contralateral knee (measured preoperative to postoperative) will be expressed in millimeters. To reduce inter-rater variability, all measurements will be performed by two unblinded, experienced physiotherapists, each with over 10 years of experience in arthrometric laxity assessment following ACL injury and reconstruction.

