#### Graft failure, revision ACL-R and other adverse events

Participants will be followed longitudinally for a period of 10 years to monitor ACL graft failure (recurrent instability requiring revision), ACL re-rupture rates, and other adverse event affecting outcome (contralateral ACL rupture, infection or septic arthritis, bleeding, and any reoperation performed during the study period). Clinical and surgical records will be reviewed, and participants will be contacted periodically according to Table 1 to assess their knee health and report any additional surgeries or injuries. This long-term follow-up aims to evaluate the durability of ACL-R and identify factors associated with graft failure and re-rupture, such as patient demographics, activity levels, or surgical techniques. At the 5- and 10-year follow-ups, any undocumented events will be retrospectively collected via the Swedish National Knee Ligament Register (SNKLR).

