#### Statistical analysis

The statistical analysis will be conducted using SPSS software (version 29.0 or updated version). Descriptive statistics, including frequency, mean, and standard deviation, will be computed for all variables, and normal distributions will be assessed using histograms, Q-Q plots and Kolmogrov-Smirinov test. Continuous variables will be compared using parametric or non-parametric methods, depending on data distribution. Categorical variables will be analysed using Pearson’s chi-square test or Fisher’s exact test.

For anterior knee laxity measurements (KT-1000), mean ± standard deviation and median (range) values will be reported. A variance-based statistical test will be used to compare, preoperative and postoperative anterior knee laxity, as well as ATT reduction between treatment groups. The choice of test will be determined based on the distribution and characteristics of the data after collection. Adjustments for baseline values may be included as part of a secondary analysis to ensure robust comparisons.

Postoperative STS values in knee laxity will be categorized and presented in three groups according to the IKDC form: Normal ≤ 2 mm (A), nearly normal 3–5 mm (B), and abnormal > 5 mm (C and D) [10, 11, 56]. The postoperative side-to-side (STS) difference will be dichotomized as either normal (≤ 5 mm) or failure (> 5 mm). Distributions and proportions of failures will be compared between intervention groups using Pearson’s chi-square test.

The study will employ both intention-to-treat (ITT), and per-protocol (PP) to ensure robust assessment of outcomes for each surgical group. The ITT analysis will include all randomized patients in their originally assigned groups, regardless of any protocol deviations or dropouts. Missing data for the ITT analysis will be managed using imputation methods where necessary. The PP analysis will include only those patients who fully adhered to the study protocol, completing their assigned surgery and primary outcome assessments.

Secondary outcomes will be evaluated across follow-up timepoints (Table 1). Continuous outcomes will be analyzed using a variance-based statistical test to assess within-group changes over time. Adjustments for baseline values may be included as part of a secondary analysis to ensure robust comparisons. Individual time points will be assessed using independent samples t-tests or non-parametric test, depending on the distribution of the data.

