Categorical outcomes will be analyzed using Pearson’s chi-square or Fisher’s exact tests. Logistic regression may also be used to adjust for potential confounders when analyzing binary outcomes. Time-to-event outcomes, such as graft failure and return to sport, will be analyzed using Kaplan–Meier survival curves and Cox proportional hazards regression models, assuming the proportional hazards assumption is met.

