Following various outcome after ACL-R over time in both QT-B and ST autograft groups is also crucial for assessing short-term and long-term consequences of graft selection. Functional tests and RTS may provide insight into the early recovery and performance, while graft failure or contralateral injury reflects the durability and risk of new injuries. Although this trial is not designed to evaluate long-term outcomes, it may provide some insights into the long-term effects of different autografts in athletes aiming to return to sport.

Study limitations include the unblinded design for patients that were deemed unfeasible, for both orthopaedic surgeons and physiotherapists involved in patient care. Additionally, loss to follow-up and missing data are potential risks in prospective studies that the study team intends to minimize and that will be accounted for in data analysis. While this study focuses on patients with a TAS ≥ 7 with the desire to go back to the same level of sport, this subgroup was selected due to the sporting demands placed on the ACL graft. We do not claim that findings will universally apply to all ACL patients, and we understand that this may limit generalizability to lower-activity populations. However, we aim to generate insights that may contribute to evidence-based clinical decision-making and graft selection in athletic populations. Another limitation is that neither preoperative nor postoperative rehabilitation will be formally monitored or recorded. However, both follow standardized protocols routinely applied in our clinical practice.

Finally, the decision not to stratify randomization by sex could introduce imbalance between groups. However, the use of simple randomization is considered methodologically sound, with minimal risk of meaningful imbalance when sample sizes are 200 participants or larger [34, 60]. We plan to adjust for important covariates in the statistical analysis if imbalances are observed at baseline [60].

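### The per-protocol set requires a completed 6-month KT-1000; if it is used for outcomes counted from surgery, it can drop early events together with the participants who had them

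*Protocol article*

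**What the plan says.** All references are to the protocol article.

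- **Two analyses (Statistical analysis).** "The study will employ both intention-to-treat (ITT), and per-protocol (PP) to ensure robust assessment of outcomes for each surgical group". The sentence speaks of outcomes generally, and the section does not rank one analysis above the other.
- **ITT set (same section).** "The ITT analysis will include all randomized patients in their originally assigned groups, regardless of any protocol deviations or dropouts".
- **PP set (same section).** "The PP analysis will include only those patients who fully adhered to the study protocol, completing their assigned surgery and primary outcome assessments". No second PP definition is given for any other endpoint.
- **Primary outcome assessments (Knee Laxity at 6 months post ACL-R).** "Knee Laxity will be measured preoperatively and at 6 months postoperatively". The measure is the difference between the injured knee and the healthy contralateral knee.
- **Time-to-event outcomes (Statistical analysis).** "Time-to-event outcomes, such as graft failure and return to sport, will be analyzed using Kaplan–Meier survival curves and Cox proportional hazards regression models". No analysis set is named here.
- **Events (Graft failure, revision ACL-R and other adverse events).** Graft failure, re-rupture, contralateral ACL rupture, infection, bleeding and reoperation are followed for 10 years, through records, periodic contact and the national register.
- **Rehabilitation.** The Postoperative rehabilitation section says: "Although adherence to the rehabilitation program will not be tracked". The Discussion lists as a limitation that "neither preoperative nor postoperative rehabilitation will be formally monitored or recorded".

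**The concern.** A PP set is normally fixed by what was done to the participant. This one also depends on something that happens six months later. For 6-month laxity that is harmless, because a laxity analysis without imputation needs the reading anyway. For outcomes whose clock starts at surgery, it means selecting participants on a post-surgery event that may itself be a consequence of the outcome. Someone who has an early failure, infection or reoperation and so has no valid 6-month reading is removed from both the numerator and the denominator.

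Two things are at stake. PP event rates can be too low, and the PP contrast can shift if such losses are more common in one arm. The second matters because hypothesis 7 predicts no difference in graft failure or contralateral rupture, and losing more events from the arm with more of them moves the PP result toward that prediction.

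A smaller issue lies in the same sentence. Calling these participants fully adherent could be taken to cover rehabilitation, for which the trial holds no adherence data.

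**Working it through.** The plan states no event rate and no share of participants expected to miss the 6-month test, so there is no figure of its own to reproduce on this point. The check has three parts.

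**1. When is PP membership decided?** The PP rule requires the primary outcome assessments. These are KT-1000 before surgery and at 6 months. Membership therefore cannot be known before 6 months.

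**2. Which outcomes can an early event remove?**
- *Graft failure, infection, reoperation:* lost from PP only if the participant has no valid 6-month reading. The article does not say whether such participants are tested, or whether a reading after an early revision counts.
- *Contralateral rupture:* the link is tighter. The primary measure needs a healthy contralateral knee. A rupture there before 6 months removes the comparator, so the assessment can no longer be completed as defined.

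**3. How large could the effect be?** Inputs: N = 100 per arm (Intervention section). All event counts below are assumptions. Let e be failures before 6 months, l later failures, and m the share of early failures without a valid 6-month reading. Assume nobody else leaves the PP set.

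- ITT proportion = (e + l) / N
- PP proportion = (e(1 − m) + l) / (N − e·m)

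*Case A: early failures 3 vs 1, later failures 5 vs 5.* ITT: 8/100 = 8.0% vs 6/100 = 6.0%, ratio 1.33.

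| m | Arm 1 PP | Arm 2 PP | Ratio |
|---|---|---|---|
| 0 | 8/100 = 8.0% | 6/100 = 6.0% | 1.33 |
| 0.5 | 6.5/98.5 = 6.6% | 5.5/99.5 = 5.5% | 1.19 |
| 1 | 5/97 = 5.2% | 5/99 = 5.1% | 1.02 |

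*Case B: early failures 2 vs 2, later failures 5 vs 5, same m in both arms.* ITT is 7.0% in each arm. PP is 7.0% at m = 0, 6/99 = 6.1% at m = 0.5, and 5/98 = 5.1% at m = 1. The ratio stays at 1.00 and only the level falls.

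*Case C: as B, but m = 0 in one arm and m = 1 in the other.* PP is 7/100 = 7.0% vs 5/98 = 5.1%, ratio 1.37, although ITT shows no difference.

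So the effect runs from nothing (m = 0), through a lower level with an undistorted ratio (equal losses), to a distorted ratio in either direction (unequal losses).

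**The case against.** Several counter-arguments have force.

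- **PP graft-failure curves are inferred.** The paragraph defining ITT and PP follows the laxity paragraphs and precedes the one on secondary outcomes, and its entry condition is the primary outcome. It can fairly be read as a primary-outcome set, for which requiring the KT-1000 is natural. This stands as a limit: the article does not state that graft failure will be analysed per protocol. It does not restrict PP to laxity either.
- **A failed knee can still be measured.** A reader might infer that the rule deletes all early graft failures. The documents do not support that. Only those without a valid 6-month reading leave the set.
- **Early failures may be few.** Running typically starts at 4 to 5 months and return to sport is generally assessed at 8 to 12 months, so the 6-month test comes before most sporting exposure. This stands for graft failure. It says less about infection or reoperation, for which the article gives no timing.
- **ITT keeps everyone**, and events are collected independently of KT-1000 attendance. This stands and confines the problem to the PP analysis.
- **The adherence condition may be defined by its own second clause.** Assigned surgery and KT-1000 completion are both recorded, and rehabilitation may be tailored, so variation is not in itself a deviation. A reader might infer that the PP set cannot be built because it rests on uncollected data. That goes too far. What remains is that the label promises more than these two items verify.
- **Endpoint-specific sets are often left to the analysis plan**, which is not at hand. That would excuse silence, but here the article states a rule in general terms.

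**Conclusion.** The point holds in conditional form. As written, one PP rule serves outcomes in general and makes entry depend on a 6-month measurement. If it is applied to outcomes that start at surgery, it conditions on a post-surgery event and can lower PP event rates. It distorts the arm contrast only if the losses differ by arm.

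The size is unknown from the documents. It is zero if every participant with an early event still has a valid reading. The ratios of 1.19 and 1.02 against an ITT ratio of 1.33, and 1.37 against 1.00, rest entirely on assumed counts. A reader might also take 5 failures per 100 with 10–30% of them early, giving 5 × 0.10 = 0.5 to 5 × 0.30 = 1.5 failures lost per arm. Those rates are assumed too, and the result treats every early failure as untested.

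A reader might further infer a known imbalance between arms, because the Background names patellar fracture as a risk of the bone-block graft. The article gives no rate or timing for it and does not link it to a missed laxity test, so a differential loss is possible but not shown.

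The main ITT comparison is untouched. This is a correction worth making to the PP definition, not a threat to the trial's primary result.

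**What to change.** Replace the PP sentence with criteria that are recorded and known at surgery: the participant was eligible and the assigned graft was implanted. Then:

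1. Require the 6-month KT-1000 only for the PP analysis of 6-month laxity.
2. Run any PP analysis of time-to-event and adverse-event outcomes from surgery, in all participants who received the assigned graft, and name that set beside the Kaplan–Meier and Cox methods.
3. Drop the full-adherence wording in favour of the recorded criteria, so that nothing suggests verified adherence to rehabilitation.

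No extra clause is needed for gracilis augmentation, because the Surgical procedures section already makes it part of the semitendinosus procedure.

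The cost is a sentence or two in the protocol or analysis plan and no new data. The Trial status section expects completion for the 6-month analysis in the second half of 2026 or early 2027, so the change can be made before that analysis. The downside is that the PP set becomes larger and differs less from ITT, so it contributes less as a separate check.

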Following various outcome after ACL-R over time in both QT-B and ST autograft groups is also crucial for assessing short-term and long-term consequences of graft selection. Functional tests and RTS may provide insight into the early recovery and performance, while graft failure or contralateral injury reflects the durability and risk of new injuries. Although this trial is not designed to evaluate long-term outcomes, it may provide some insights into the long-term effects of different autografts in athletes aiming to return to sport.

Study limitations include the unblinded design for patients that were deemed unfeasible, for both orthopaedic surgeons and physiotherapists involved in patient care. Additionally, loss to follow-up and missing data are potential risks in prospective studies that the study team intends to minimize and that will be accounted for in data analysis. While this study focuses on patients with a TAS ≥ 7 with the desire to go back to the same level of sport, this subgroup was selected due to the sporting demands placed on the ACL graft. We do not claim that findings will universally apply to all ACL patients, and we understand that this may limit generalizability to lower-activity populations. However, we aim to generate insights that may contribute to evidence-based clinical decision-making and graft selection in athletic populations. Another limitation is that neither preoperative nor postoperative rehabilitation will be formally monitored or recorded. However, both follow standardized protocols routinely applied in our clinical practice.

Finally, the decision not to stratify randomization by sex could introduce imbalance between groups. However, the use of simple randomization is considered methodologically sound, with minimal risk of meaningful imbalance when sample sizes are 200 participants or larger [34, 60]. We plan to adjust for important covariates in the statistical analysis if imbalances are observed at baseline [60].

### Trial status

The inclusion of the first participant was on February 10, 2020, and the first intervention took place on May 13, 2020. Our intention was to prospectively register this trial and to fulfill the ICMJE guidelines, thus the trial was registered at ClinicalTrials.gov on February 6, 2020, prior to the inclusion of the first participant. However, a technical delay led to the protocol not being released for review until February 26, 2020, and not making it publicly available until March 4, 2020. Although the trial started at the beginning of the COVID-19 pandemic, it has continued and had a steady recruitment during and after the COVID-19 public health emergency. We have until now recruited 170 participants and hope to finalize inclusion at the end of 2025 or beginning of 2026. The estimated primary study completion date for 6 months analysis is therefore around the second half of 2026 or beginning of 2027.

## Data Availability

No datasets were generated or analysed during the current study.

## Abbreviations

ACL: Anterior cruciate ligament
ACL-R: Anterior cruciate ligament reconstruction
ACL-RSI: Anterior cruciate ligament Return to Sports Injury scale
ADL: Activity daily living
ATT: Anterior tibial translation
BPTB: Bone-patellar tendon-bone
DMC: Data Monitoring Committee
EQ-5D: European Quality of Life 5 dimension score
HT: Hamstrings tendon
ICMJE: International Committee of Medical Journal Editors
ICRS: International Cartilage Repair Society Classification
IKDC-SKF: International Knee Documentation Committee Subjective Knee Form
KOOS: Knee Osteoarthritis and Outcome Scores
LSI: Limb symmetry index
MRI: Magnetic resonance imaging
OA: Osteoarthritis
PROM: Patient reported outcome measure
RCT: Randomized clinical trial
OSTRC: Oslo Sports Trauma Research Center
ROM: Range of motion
QT: Quadriceps tendon
SPIRIT: Standard Protocol Items Recommendations for Interventional Trials 2013 Statement
QoL: Quality of Life
ST: Semitendinosus tendon
STS: Side to side
